#### Treatment diaries

Participants will be provided with a treatment diary at the same time as their medication pack is dispensed and blood samples will be collect at baseline. All medications other than the trial treatment taken during the treatment phase of the study will be recorded in a treatment diary. This will include prescription and non-prescription treatment, such as oral analgesics, contraceptives, vitamins, topical preparations and herbal preparations.

#### Participant log

We will keep an anonymised electronic log of women who fulfil the eligibility criteria, women who are invited to participate in the study, women recruited and women who leave the trial early. Reasons for non-recruitment (e.g. non-eligibility, refusal to participate, administrative error) will also be recorded. We will attempt to collect reasons for non-participation from women who decline to take part after previously providing contact details. During the course of the study, we will attempt to document reasons for withdrawal from the study and loss to follow-up.

### Termination of study

The blinding code will only be broken in emergency situations for reasons of patient safety, where knowledge of the treatment administered is necessary for the treatment of a serious adverse event or when required by local regulatory authorities. Participants whose randomisation codes are broken will cease treatment, but will continue to be followed up. The principal investigator will document the reason for breaking the blind in the participant’s source documents and in the Investigator Site Master File. If the participant requires to be unblinded in an emergency, then the research team or pharmacy should be contacted.

### Adverse events

Participants will collect information about adverse events in their treatment diaries. They will also be instructed to contact the clinical research fellow at any time after consenting to join the trial if they have an event that requires hospitalisation or an event that results in persistent or significant disability or incapacity. Omega-3 PUFA are an FDA-approved dietary supplement, and serious adverse events are not anticipated. Any serious adverse events that occur after joining the trial will be reported in detail in the participant’s medical notes, followed up until resolution of the event and reported to the Academic and Clinical Central Office for Research & Development (ACCORD) Research Governance (http://www.accord.ed.ac.uk) and Quality Assurance Office based at the University of Edinburgh immediately, or within 24 h. ACCORD will onward report all serious adverse events (SAE) within 7 days. Hospitalisation for a pre-existing condition, e.g. exacerbation of pain due to endometriosis will not be considered a SAE, but will be documented.

### Sample size

The emphasis in this study is to establish feasibility, not statistical significance. This study is designed primarily to explore the recruitment and retention rates, and we will aim to recruit as many women as possible over a 12-month period. We estimate that we will recruit ~ 4–5 patients per month and will aim to recruit 40 patients. As we anticipate a recruitment rate of 50%, 40 participants would be able to give 95% confidence interval of 35–65%. The data from this pilot study will be used to refine sample size calculations for any future RCT.

### Data analysis

#### Recruitment and retention rates

Using the information collected from the participant log, we will determine the number of patients recruited from the pool of eligible women and a > 50% recruitment will be deemed acceptable. While a retention rate of 100% would be ideal, we will consider a rate of 80% satisfactory. We will provide an estimate of the proportion and its 95% confidence interval. In addition, we will determine the nature and number of unanswered questions in each questionnaire. We aim to determine whether the trial design will perform well enough in the field to warrant rolling out the study to full trial. All analysis will be carried out at the University of Edinburgh.

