### Primary objective

The primary objective is to assess recruitment and retention rates. Recruitment is defined as the proportion of eligible patients who agreed to participate from the number approached. Whereas retention is defined as the proportion of the participating patients who completed both baseline and follow-up visits.

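### The only recruitment benchmark, uptake above 50%, is not met by the plan's own 50% scenario and, measured against women approached, takes no account of how many women are recruited

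*Protocol article*

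**What the plan says.** Recruitment and retention rates are the co-primary outcomes. Under Primary objective, "Recruitment is defined as the proportion of eligible patients who agreed to participate from the number approached". Under Data analysis, subsection Recruitment and retention rates, the wording is different: "we will determine the number of patients recruited from the pool of eligible women". The same sentence sets the benchmark, "a > 50% recruitment will be deemed acceptable". Retention has its own benchmark of 80%. A 95% confidence interval is to be reported, but it is not linked to either benchmark.

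Sample size gives the planning figures: "We estimate that we will recruit ~ 4–5 patients per month and will aim to recruit 40 patients", over a 12-month window, and "As we anticipate a recruitment rate of 50%, 40 participants would be able to give 95% confidence interval of 35–65" per cent. The target and the monthly rate appear there as an aim and an estimate. Neither is given an acceptability threshold anywhere in the article.

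The purpose of the benchmarks is stated in the same analysis subsection: "We aim to determine whether the trial design will perform well enough in the field to warrant rolling out the study to full trial".

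**The concern.** Two features of the benchmark fit badly with the rest of the plan.

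First, the value that the plan expects lies exactly on a cut-off that it must exceed. A pilot that reaches its target and confirms its assumption would then report recruitment that falls short of the stated standard.

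Second, the benchmark is a proportion with no count or rate attached. The future trial is to be multicentre, and its number of centres and duration depend on how many women a centre recruits and randomises per month. Uptake does not supply that. Under Participant enrolment, consultants must first give permission, and women must agree to be seen by the trial team, before anyone is approached. If the denominator is women approached, losses at those two steps never enter the rate, so uptake can look good while accrual is poor.

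**Working it through.** **Inputs.** Anticipated uptake 50%, target 40 women, 12 months and about 4–5 women per month (Sample size); benchmark strictly above 50% (Recruitment and retention rates); denominator women approached (Primary objective).

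**1. The plan's own interval.** With p = 0.50 and n = 40, the Wald interval is 0.5 ± 1.96 × √(0.25/40) = 34.5–65.5%, and the Wilson interval is 35.2–64.8%. The stated 35–65% is reproduced, but with 40 as the denominator. Under the Primary objective definition, 40 women recruited at 50% means 40/0.50 = 80 approached, with a Wald interval of 39.0–61.0%. Both denominators are carried below.

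**2. Planning scenario against the benchmark.** 40/80 = 50.0%, which is not above 50%. With 40 approached, 20/40 = 50.0% and the result is the same.

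**3. Chance of meeting the benchmark when the true uptake is 50%.** For an even n, P(observed > 50%) = (1 − P(X = n/2))/2.
- n = 80: (1 − 0.0889)/2 = 0.456, so it is missed about 54% of the time.
- n = 40: (1 − 0.1254)/2 = 0.437.

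**4. How much is due to the strict sign.** With 'at least 50%' and n = 80, the chance is 0.456 + 0.089 = 0.544. The sign therefore accounts for about 9 percentage points. The rest comes from placing any cut-off at the expected value. With 80 approached, the true uptake would have to be about 55% for an 80% chance of exceeding 50%.

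**5. Volume.** The target needs 40/12 = 3.3 women per month, and the stated 4–5 per month would give 48–60 in 12 months. As an illustration, take 12 recruited of 20 approached over the year. Uptake is 12/20 = 60% (exact 95% CI about 36–81%), so the benchmark is met. Accrual is 12/12 = 1 woman per month, and the shortfall is (40 − 12)/40 = 70%.

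**6. Effect of the denominator on step 5.** If the denominator is instead all eligible women, those never approached are counted. The same 12 recruits stop meeting the benchmark once the pool reaches 24 (12/24 = 50%), that is, once four eligible women were not approached. The verdict on identical accrual can therefore depend on which of the two definitions is used.

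**The case against.** A reader might infer that a pilot reaching its target could be declared infeasible. The text does not support that. It says that uptake above 50% is acceptable and nowhere says that a lower rate stops the programme. The judgement about a full trial also draws on retention, the confidence interval, unanswered questions, acceptability and compliance, and the sample size section describes the rates as something to explore. This stands, and it limits the consequence.

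A reader might also infer that women who are never approached cannot affect the rate, so that a very small pilot would always slip through. That holds only under the Primary objective definition. Under the pool of eligible women they lower the rate, as step 6 shows. This stands too, but it exposes a conflict between two sections and does not supply a volume criterion: neither definition sets a minimum number.

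It is fair to add that a benchmark equal to the expected value is a choice, that changing the sign alone gains little, and that a shortfall against 40 would be visible from the participant log and a wide interval. But visibility is not a criterion, and the analysis section would still call the 12-of-20 result acceptable.

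Finally, this is a condensed article, and fuller progression criteria may exist elsewhere. That would answer a complaint about missing detail. It does not answer a threshold and a planning value that conflict on the page, or two stated denominators.

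**Conclusion.** The concern holds in a limited form. The benchmark is not met by the plan's own scenario (40/80), and at a true uptake of 50% with 80 women approached it is met about 46% of the time (44% if 40 are approached). With women approached as the denominator it is silent on volume, so a pilot 70% below target could be called acceptable. The two denominators conflict and must be reconciled.

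The probabilities assume that women decide independently with a common true uptake of 50%. The 12-of-20 case is an illustration and not a forecast. The result is a co-primary benchmark that can mislead in either direction. It is not an automatic stop, and it has no bearing on participant safety or on what data are collected. It should be changed, because the benchmark feeds the decision on a full trial.

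**What to change.** In Data analysis, Recruitment and retention rates:

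- Use one denominator: women approached, as under Primary objective. Report eligible women who were not approached separately from the participant log.
- Make the uptake benchmark consistent with the anticipated 50%: at minimum 'at least 50%', read with its 95% confidence interval and not as a strict cut-off at the expected value. A lower cut-off, or a middle zone for amending the design and proceeding, is a matter of preference.
- Add a second condition: recruitment is acceptable only if accrual delivers the stated target of 40 women recruited in 12 months (3.3 per month).
- Report women consented and women randomised per month separately. The target is stated as women recruited, and the four-week run-in with its pain-score requirement lies before randomisation, so the two counts can differ.

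The cost is mainly wording. The log already covers eligible, invited and recruited women; monthly figures also need consent and randomisation dates. No extra visits or participants are needed. The downside is a second condition that the pilot could miss.

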#### Effectiveness and acceptability of proposed methods of recruitment, randomisation, treatments and assessment tools

These areas will be assessed quantitatively using additional questions included in participant questionnaires administered at 8 weeks. The data collected from the different questionnaires will be used to explore comparisons between the two groups and will be reported as estimates of difference and corresponding confidence intervals in order to calculate sample size. Due to the conflicting literature about the benefits of methods such as prescription monitoring, pill counting and devices for monitoring the self-administration of medicines, data on blinding and compliance to treatment will be derived from questionnaires at 8 weeks. We aim to determine if treatment is acceptable in terms of self-reported compliance (from treatment diaries). We will examine the effect of non-compliance and retention, which will be used to inform the sample size required for a full trial.

### Trial sponsors

The trial is co-sponsored by the University of Edinburgh and NHS Lothian.

### Data handling, storage and archiving

A log with the patients’ name and date of birth will be kept along with their unique study number in a separate file. All the data generated from the study will be stored in an anonymised form in a bespoke database, which will also be password protected. Only anonymised information will be stored on this, and participants will only be identifiable by their study number. All paperwork will be kept in a locked filing cabinet in a locked office. All the data will be stored on university server on a password-protected computer with a limited access to the research team, in accordance with the NHS and University of Edinburgh guidelines and in accordance with the Data Protection Act. All study documentation will be kept for a minimum of 5 years from the protocol defined end of study point. When the minimum retention period has elapsed, study documentation will not be destroyed without permission from the sponsor. The trial statistician will also be blinded to the treatment during analysis.

### Ethics

Ethical approval has been obtained from the Scotland A Research Ethics Committee (LREC 16/SS/0010).

### Dissemination

The data will be presented at international conferences and published in peer-reviewed journals. The clinical study report will be used for publication and presentation at scientific meetings. We will make the information obtained from the study available to the public through national bodies, e.g. Endometriosis UK.

## Discussion

We believe that a definitive evaluation of the efficacy of Omega-3 PUFA in the management of endometriosis requires a multicentre randomised controlled trial. Recognising that there may be potential difficulties in mounting a large randomised controlled trial for the management of endometriosis-associated pain using a supplement which is widely available over the counter, we have designed this pilot study to assess practical feasibility following the Initiative on Methods, Measurement, and Pain Assessment in Clinical Trials (IMMPACT) recommendations for the design of chronic pain clinical trials [20]. We plan to randomise participants to either Omega-3 PUFA or olive oil and then evaluate recruitment and retention rates as our primary outcome.

A potential limitation of our study is the broad inclusion and exclusion criteria which we have produced in an attempt to reflect the true clinical scenario of endometriosis. Our criteria do not take into account pain intensity, do not exclude women with non-reproductive comorbidities (e.g. irritable bowel syndrome, bladder pain syndrome) that could explain their symptoms and allow participants the use of concomitant medications. We are aware that these characteristics may increase variability in patient responsiveness to treatment and carry the risk of failing to demonstrate treatment effect. We will therefore capture this information in our pilot study in the participants’ questionnaires and treatment diaries to inform interpretation of our results and the planning of the future randomised controlled trial. Like many of the medications/supplements used for endometriosis, Omega-3 PUFA given in the highest effective dose with the rate and severity of adverse effects are minimised.

One of the other limitations of our pilot study is the lack of availability of a suitable placebo. It was not possible to find a placebo identical to Omega-3 PUFA, and therefore, we decided to use a ‘comparator’ (olive oil) instead of a true placebo. We thought that olive oil, a comparator with the potential for pain relief [21], was the best option for our target population to encourage participation in our trial [22]. The drawback of using olive oil is that it may have a unique taste and there is a theoretical risk of the subjects guessing which arm of the trial they have been randomised to. In order to determine whether significant ‘unblinding’ was present, we will ask the subjects at the conclusion of the trial to guess what treatment was received and the primary reason for the guess in an attempt to determine the validity of using olive oil as a suitable comparator. Another limitation of our study is the short timescale of the treatment phase, and we are aware that a longer trial will likely be necessary to better assess the long-term effects of Omega-3 PUFA.

We have chosen data collection tools to assess the core domains of pain, physical/emotional functioning (including sleeping difficulties), improvement/satisfaction with treatment, symptoms and adverse events, following advice from a clinical psychologist and a general practitioner, both with a research interest in endometriosis. These tools are in line with the IMMPACT recommendations for chronic pain trials [23]. We will assess the reliability and acceptability of these data collection tools in order to refine our methods for the subsequent RCT.

In summary, this pilot trial with embedded evaluation of trial processes and collection of outcome data will allow us to undertake detailed feasibility work to inform a future large-scale trial in the important but challenging area of dietary supplements and endometriosis-associated pain.

## Abbreviations

AA: Arachidonic acid
ACCORD: Academic and Clinical Central Office for Research and Development
BFI: Brief Fatigue Inventory
BPI: Brief Pain Inventory
CRF: Case report form
DHA: Docosahexaenoic acid
EPA: Eicosapentaenoic acid
FDA: Food and Drug Administration
GHQ-12: General Health Questionnaire-12
IMMPACT: Initiative on Methods, Measurement, and Pain Assessment in Clinical Trials
NRS: Numerical Rating Pain Score
PCQ: Pain Catastrophizing Questionnaire
PUFA: Purified fatty acids
RCT: Randomised controlled trial
SAQ: Sexual Activity Questionnaire
SF-12: 12-Item Short-Form Health Survey
WPAI-SHP: Work and Productivity Impairment Questionnaire-specific Health Problem Version 2.0
